### Study population

The study will evaluate patients with GEJ type II carcinoma whose tumor can be safely resected by both transthoracic esophagectomy and transhiatal extended gastrectomy. In detail, the inclusion criteria are:
Histologically proven adenocarcinoma of the GEJ type IIResectable by both transthoracic esophagectomy and transhiatal extended gastrectomy according to the local surgical investigatorPre-treatment stage cT1-4a, N0–3, M0In case of stage cT4a, curative resectability must be explicitly verified by the local surgical investigator prior to randomizationCompletion of all four cycles of chemotherapy (FLOT) preoperatively, in case of locally advanced tumors (cT3-T4 or N+)Age ≥ 18ECOG Eastern Cooperative Oncology Group (ECOG) performance status 0–2ASA < 4.Adequate bone marrow function (white blood cells > 3 × 10^9 /l; hemoglobin > 9 g/dl; platelets > 100 × 10^9 /l), renal function (glomerular filtration rate > 60 ml/min), and liver function (total bilirubin < 1.5x upper level of normal (ULN), aspartate transaminase (AST) < 2.5x ULN and alanine transaminase (ALT) < 3x ULN)Written informed consent

The exclusion criteria are:
Histologically proven adenocarcinoma of the GEJ type I and IIITumor resectable only by transthoracic esophagectomy or only by transhiatal extended gastrectomy, according to the local surgical investigatorTumor expanding more than 5 cm proximal of the GEJPositive lymph nodes only resectable by transthoracic esophagectomy (i.e. in the mid-upper mediastinum) or only resectable by transhiatal extended gastrectomy according to the local surgical investigator.Clinically significant (active) cardiac disease (i.e. symptomatic coronary artery disease or myocardial infarction within last 12 months), resulting in a left ventricular ejection fraction < 50% (determined by echocardiography)Clinically significant lung disease (forced expiratory volume in one second (FEV1) < 1.5 l/s)Pregnant women and nursing mothers

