### Sample size calculation

The primary endpoint is overall survival. We assume a cumulative survival after 2.5 years of 45% for transthoracic esophagectomy and 30% for transhiatal extended gastrectomy (see Fig. 1c in [20]). This corresponds to a hazard ratio of 0.663. A total of 188 events need to be observed to detect this difference with the stratified log-rank test (two-sided type I error 5%, power 80%, accounting for the interim analysis according to two-sided symmetric O’Brien-Fleming type alpha-spending at 94 events). Thus, 262 patients need to be enrolled and followed up (assuming 2,5 years of accrural, 5 years of follow-up and 5% censoring per year) [21]. For the key secondary outcome R0 resection Parry et al. report percentages of 87 and 71%, respectively [20]. This corresponds to an odds ratio of 2.73. Thus, 262 enrolled patients are also sufficient to give the stratified Mantel-Hanszel test at least 80% power (two-sided type I error 5%). Before participating in the trial, each center reported possible recruitment figures based on the number of patients with GEJ type II tumors in recent years. Screening will continue until the target sample size is achieved.

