### Statistical analysis

The primary analysis will be performed on the full analysis set (intention-to-treat) and comprises all patients with written informed consent and who were operated. The analysis is as assigned by stratified randomization (i.e. site or surgeon and tumor stage). The primary outcome of overall survival will be evaluated by the stratified log-rank test and is event-driven (i.e. following observation of 188 events). The hazard ratio with 95% confidence interval (CI) is estimated by stratified Cox regression. The assumption of non-informative censoring is examined using standard approaches (i.e. Kaplan-Meier curves, examining patterns of censoring across covariates and association between censoring and covariates). The key secondary outcome R0 resection rate is analyzed by comparing the corresponding odds between treatment groups with the stratified Mantel-Haenszel test. A missing assessment is counted as failure. Contingency tables of strata with “empty rows or columns” are pooled. The combined Mantel-Haenszel odds ratio with 95% CI is calculated. The potential impact of clustering associated with both interventions is addressed in a sensitivity analysis [22, 23]. The secondary outcome quality of life is averaged over 36 months (area under curve, AUC) and tested for non-inferiority of the esophagectomy arm regarding a margin of 80%. Missing values are linearly interpolated. The key outcomes overall survival, R0 resection and quality of life are tested in a fixed sequence, thus no alpha-correction is required for strong type I error control (5%, two-sided).

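### Optional gain: the primary survival test could also adjust for age and ECOG status, both known before randomization, for about 0 to 5 points of power at 188 deaths

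*Protocol article*

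**What the plan says.** The Statistical analysis section fixes the primary test: "The primary outcome of overall survival will be evaluated by the stratified log-rank test and is event-driven (i.e. following observation of 188 events". The strata come from the randomization: "The analysis is as assigned by stratified randomization (i.e. site or surgeon and tumor stage". The effect estimate uses the same structure: "The hazard ratio with 95% confidence interval (CI) is estimated by stratified Cox regression". No further covariate is named for either.

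The Sample size calculation section sizes the trial for this same test. Its inputs are "We assume a cumulative survival after 2.5 years of 45% for transthoracic esophagectomy and 30% for transhiatal extended gastrectomy", then "This corresponds to a hazard ratio of 0.663", and the error rates are "two-sided type I error 5%, power 80%, accounting for the interim analysis according to two-sided symmetric O’Brien-Fleming type alpha-spending at 94 events". The result is: "A total of 188 events need to be observed to detect this difference with the stratified log-rank test".

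The Study population section sets a minimum age of 18 and requires "Eastern Cooperative Oncology Group (ECOG) performance status" 0 to 2. Under Patient inclusion and randomization, eligibility is validated before randomization. Table 1 records demography at V0 and the inclusion and exclusion check at V1. It has no separate row for the ECOG grade.

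**The concern.** Leaving a prognostic baseline variable out of a survival comparison pulls the estimated hazard ratio toward 1 and costs power, even in a perfectly randomized trial. Site or surgeon and tumor stage are already in the strata; age and ECOG are not. The design aims at 80% power with no stated reserve. Overall survival also comes first in a fixed testing sequence, so a missed primary result blocks the confirmatory tests of R0 resection and quality of life. If age and ECOG carry prognostic information within strata, the trial could use it without one more patient or death.

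The power argument concerns the log-rank test, not the Cox sentence. Adding covariates to the Cox model alone would leave the primary test as it is.

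**Working it through.** **1. The plan's own figure.** Inputs from the Sample size calculation section: survival of 45% and 30% at 2.5 years, two-sided 5%, power 80%, one O'Brien-Fleming type interim at 94 of 188 events.

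- HR = ln(0.45)/ln(0.30) = 0.7985/1.2040 = 0.663, so ln HR = −0.4107.
- Schoenfeld without interim: 4 × (1.960 + 0.842)² / 0.4107² ≈ 186 events.
- With Lan-DeMets O'Brien-Fleming spending at half the information (critical values 2.772 and 1.979): 187.8, so 188 events. Power at 188 is 80.04%.

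The stated 188 events and 80% power reproduce.

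**2. What is assumed.** The article does not give the prognostic strength of age or ECOG, so a range is used. ECOG 0/1/2 is taken as 50/40/10%, which has variance 0.4 × 1 + 0.1 × 4 − 0.6² = 0.44. The SD of the log hazard explained by both is √[(ln HR per SD of age)² + 0.44 × (ln HR per ECOG point)²]:

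- weak (1.1 and 1.2): √(0.0091 + 0.0146) = 0.15
- moderate (1.2 and 1.4): √(0.0332 + 0.0498) = 0.29
- strong (1.3 and 1.7): √(0.0688 + 0.1239) = 0.44

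**3. Simulated power of the test proposed below.** There were 3,000 trials per setting, analyzed at 188 deaths with the final critical value 1.979. The two columns of strata are stage alone (two levels), and 12 sites by two stage levels. Twelve is the number of centers selected under Trial status; two stage levels and equal sites are assumptions.

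| Age and ECOG effect | Stage strata: planned vs adjusted | 12 sites × 2 stages: planned vs adjusted |
|---|---|---|
| none | 78.3 vs 78.8% | 73.0 vs 73.4% |
| weak | 78.8 vs 79.6% | 73.9 vs 74.3% |
| moderate | 80.0 vs 81.5% | 73.0 vs 74.3% |
| strong | 79.9 vs 84.4% | 75.8 vs 79.4% |

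The gains are +0.5, +0.8, +1.5 and +4.5 points with stage strata, and +0.4, +0.4, +1.3 and +3.6 with site-by-stage strata. Each single power figure has a Monte Carlo standard error of about √(0.8 × 0.2/3000) = 0.7 points; the paired differences are more precise. A second simulation of the same test gave about 0 (none), +0.5 to +1 (weak), +1.5 to +2 (moderate) and +3.5 to +5 (strong). Type I error in the strong case was 5.6 vs 5.3% (stage) and 4.6 vs 4.7% (site by stage), so adjustment does not change it.

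**4. What the gain is worth.** Equivalent events = 188 × [(1.979 + z)/(1.979 + 0.842)]², where z is the normal quantile of the power reached. A rise from 80% to 82% (z = 0.915) corresponds to about 198 events, or 10 more deaths. A rise to 85% (z = 1.036) corresponds to about 215, or 27 more.

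**5. Effect on the hazard ratio.** When age and ECOG were added to the stratified Cox model in simulation, the mean hazard ratio moved from about 0.66 to between 0.66 (weak) and 0.63 (strong). The adjusted ratio is conditional on these covariates and answers a slightly different question from the planning value of 0.663.

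**The case against.** The strongest reply is that the plan is coherent. Randomization, test and sample size all rest on the same stratified log-rank test, which is a standard primary analysis, and it delivers its stated power. That stands in full. A reader might infer that the trial is underpowered because age and ECOG are missing. The documents do not support this, because the 80% was calculated for the planned test and reproduces. The lower simulated power with 12 sites by two stages comes from thin strata under assumed site sizes and is not caused by omitting covariates.

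The second reply is that the size of the gain is unknown and may be close to zero. Stage is already stratified, and the fitness criteria may narrow the spread of prognosis. This stands too. A reader might expect 4 to 12 points, because an unstratified Cox model tested at 1.96 gives gains from 3.7 points (79.4 to 83.1%, explained SD 0.3) to 12.3 (80.1 to 92.4%, SD 0.7). That comparison omits the strata and the interim adjustment, and it is not the test proposed here. Its upper end also assumes stronger covariates than the strong case above.

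Third, the change is not free. Table 1 has no ECOG row, so a stored grade of 0, 1 or 2 is an inference from the eligibility criterion. Recruitment had begun, and modifications that affect the trial return to ethics review. This means a small cost, not none.

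Fourth, an adjusted hazard ratio is a different quantity. That is a good reason not to replace the planned estimate. It does not count against the adjusted test, whose null hypothesis is that of the stratified log-rank test.

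Finally, an analysis plan that is not shown may contain adjusted supportive analyses. These would not change the power of the primary test, which the article itself fixes.

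**Conclusion.** This is an optional, inexpensive improvement and not a defect. Adjusting the primary test for age and ECOG gains about 0 to 5 points of power at 188 deaths: essentially nothing if they are not prognostic, up to 1 point if weakly so, about 1 to 2 if moderately, and about 3.5 to 5 if strongly. Type I error is unchanged, and no simulated setting of this test showed a material loss. The range rests on assumed prognostic effects, an assumed ECOG distribution, exponential survival and final-look critical values. The documents can neither narrow it nor show where in it this trial lies.

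**What to change.** Before the interim analysis at 94 deaths, amend the Statistical analysis section as follows:

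- Primary test at both the 94-death and 188-death looks: covariate-adjusted stratified log-rank test, same strata, with age (continuous) and ECOG (0/1/2).
- Main estimate: the stratified Cox hazard ratio with 95% CI, as now planned.
- Supportive: the stratified Cox hazard ratio adjusted for age and ECOG, and the unadjusted stratified log-rank test.
- State the covariate coding and a rule for missing values. Use no variable that becomes known only after randomization, such as pathological stage or R0 status.
- Record the ECOG grade already assessed for eligibility as its own data item.

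The cost is a few sentences, one data field and a protocol modification; no extra patients, deaths or examinations are needed. One small drawback remains: the primary test will no longer match the unadjusted Cox confidence interval exactly, so near the significance boundary the two could disagree. The text should say in advance that the test decides.

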### Patient inclusion and randomization

When baseline assessments and staging or restaging are completed, inclusion and exclusion criteria for the trial will be validated. Written informed consent will be obtained from all trial participants. Immediately after the patient has given his written consent to participate in the trial, randomization to one of the therapeutic arms will be performed by means of a 24/7 internet service based on permuted blocks of varying length, stratified by trial site and/or surgeon and tumor stage.

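### The R0 pooling rule also merges strata with an empty outcome column, which need no pooling; this pulls the Mantel-Haenszel odds ratio toward 1, slightly with 12 sites and more with surgeon-level strata

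*Protocol article*

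**What the plan says.** In the Protocol article, Statistical analysis, R0 is "analyzed by comparing the corresponding odds between treatment groups with the stratified Mantel-Haenszel test". Three sentences then set the details: "A missing assessment is counted as failure"; "Contingency tables of strata with “empty rows or columns” are pooled"; and "The combined Mantel-Haenszel odds ratio with 95% CI is calculated". R0 comes second, after overall survival, in the fixed confirmatory sequence.

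Randomization is "stratified by trial site and/or surgeon and tumor stage" (Patient inclusion and randomization), and the analysis follows the same strata. Trial status gives twelve selected centers. The article gives neither the number of stage levels nor the number of surgeons.

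Sample size calculation takes R0 rates from an earlier study ("report percentages of 87 and 71%, respectively"), adds "This corresponds to an odds ratio of 2.73", and concludes that 262 patients give the stratified test at least 80% power at a two-sided 5% level.

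The pooling sentence does not say which tables are pooled with which.

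**The concern.** The two kinds of sparse table behave differently under Mantel-Haenszel.

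- **Empty row (one arm absent).** The stratum contributes nothing as it stands, but its patients can be compared with others if it is merged. Pooling recovers information.
- **Empty column (all R0 or none R0).** Both arms have the same outcome. The stratum contributes zero to the test statistic, its variance and both odds ratio sums. This is correct behavior.

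Pooling the second kind decides from the outcome which patients keep their stratum. It also creates weight from strata that say nothing about treatment. At stake is the size of a confirmatory odds ratio: it would be reported somewhat too close to 1, by an amount that grows as strata get smaller.

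**Working it through.** **1. The plan's own figures.** OR = (0.87/0.13)/(0.71/0.29) = 6.692/2.448 = 2.73, as stated. Unstratified and with 1:1 allocation (assumed), 101 per arm give 80% power, and 131 per arm give 0.893. The claim of at least 80% is reproduced.

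**2. Mechanism.** For a stratum with a, b = R0 and non-R0 on esophagectomy, c, d = the same on gastrectomy, and total n, the odds ratio is Σ(ad/n) / Σ(bc/n). The variance term is (a+b)(c+d)(a+c)(b+d) / [n²(n−1)]. If b = d = 0 or a = c = 0, all three terms are zero.

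Take one stratum with 5/5 v 5/5 R0 and another with 0/1 v 0/1. Each contributes zero. Summed, they give a=5, b=1, c=5, d=1, n=12:
- ad/n = bc/n = 5/12, so the table's odds ratio is 1
- variance = 6·6·10·2/(144·11) = 720/1584 = 0.45

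Two uninformative strata now carry weight at an odds ratio of 1. If every pooled stratum is all R0, the pooled table still has an empty column and adds nothing. Failures must enter the pool for the pull to occur.

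**3. How sparse the strata are.** 12 sites × 2 stages gives 262/24 = 10.9 patients per stratum; 12 × 4 gives 262/48 = 5.5; 24 surgeons × 4 gives 262/96 = 2.7.

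**4. Simulation.** 3,000 trials per layout, 262 patients, gastrectomy R0 71% at the reference, within-stratum odds ratio 2.73. Assumed: blocks of 2 or 4, unequal stratum sizes, 2-4 stage levels, 24 surgeons, and baseline spread on the logit scale (site or surgeon SD / stage half-range). The odds ratio is mean numerator over mean denominator. Percentages are relative to ordinary Mantel-Haenszel.

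| Layout, spread | Ordinary | Pooled into one table | Merged within site or surgeon | Pooled table adds nothing | Power, ordinary v one table |
|---|---|---|---|---|---|
| 12×2, 0/0 | 2.734 | 2.728 (−0.2%) | 2.710 (−0.9%) | 78% of trials | 0.896 v 0.895 |
| 12×2, 0.5/0.5 | 2.752 | 2.732 (−0.7%) | 2.694 (−2.1%) | 73% | 0.893 v 0.894 |
| 12×3, 0.5/0.5 | 2.731 | 2.686 (−1.6%) | 2.646 (−3.1%) | 37% | 0.877 v 0.881 |
| 12×4, 0/0 | 2.754 | 2.711 (−1.6%) | 2.683 (−2.6%) | 19% | 0.892 v 0.897 |
| 12×4, 0.5/0.7 | 2.727 | 2.640 (−3.2%) | 2.593 (−4.9%) | 15% | 0.872 v 0.876 |
| 24×4, 0/0 | 2.747 | 2.623 (−4.5%) | 2.641 (−3.9%) | 0% | 0.857 v 0.888 |
| 24×4, 0.5/0.7 | 2.727 | 2.506 (−8.1%) | 2.541 (−6.8%) | 0% | 0.843 v 0.866 |

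Further runs that pooled either into one table or within stage gave 2.60-2.73 with 12 sites and 2.29-2.67 with 24-36 surgeons. With an extreme baseline SD of 1.2, the pull was 3% at 24 strata (2.67 v 2.74), 8% at 48 (2.53 v 2.75) and 15% at 96 (2.31 v 2.73).

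**5. What is inside the pooled table.** In the last row of the table, the average counts (a, b, c, d) are:
- two-arm empty-column strata: 40.89, 1.51, 39.88, 1.61; OR = 1.1
- one-arm strata: 11.15, 1.97, 9.09, 4.09; OR = 2.5
- sum: 52.04, 3.48, 48.97, 5.70; OR = 296.6/170.4 = 1.74

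Across layouts the three ranges were 1.05-1.11, 2.3-3.1 and about 1.2-2.1.

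**6. Type I error.** With a true odds ratio of 1, the written rule rejected in 4.1-5.0% of trials, and in 3.4-3.6% with 36 surgeons × 4 stages.

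**The case against.** The strongest case for the plan is that the article is condensed and pooling mechanics can be left to the analysis plan. On the twelve documented sites the effect is small. The larger figures need surgeon numbers that the article does not give. This stands, and it is why the point is minor. It does not remove the point, because the article itself states that empty columns trigger pooling, and the pull appears under each destination tried.

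A reader might infer four stronger things that the document does not support:

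- **That all sparse strata go into a single table across stages, discarding the stage adjustment.** The text names no destination. Pooling within stage or within site fits the sentence equally well.
- **That the pooled table as a whole sits at an odds ratio of 1.** This is nearly true of the two-arm empty-column strata only. The one-arm strata return real treatment information.
- **That the rule costs power or undermines the 80% claim.** Against ordinary Mantel-Haenszel, power was about equal with 12 sites and higher at 24×4. It was lower (0.817 v 0.837) with 96 strata and extreme spread, and still above 80%.
- **That false positives rise.** Whether a column is empty depends on the stratum's outcome total and not on the difference between arms. The error, where there is one, is conservative.

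Nor does merging good sites with each other cause dilution. All-R0 strata pooled only among themselves keep zero weight.

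**Conclusion.** The concern holds as a minor one. The stated rule pools empty-column strata that Mantel-Haenszel already handles correctly, selects them by outcome, and so attenuates the R0 odds ratio. The size is about 0-5% with 12 sites and 2-4 stage levels under none to moderate baseline differences; an extreme spread took 48 strata to 8%. It is about 5-15% with surgeon-level strata; across all surgeon layouts run, 2.67 to 2.29 against 2.73 is 2% to 16%. Stage levels, surgeon numbers, block sizes, stratum sizes and baseline spread are assumptions. The confirmatory R0 test remains valid and adequately powered. What suffers is the accuracy of the estimate and the independence of the strata from the outcome.

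**What to change.** Replace the pooling sentence with: *Strata with an empty outcome column are left as they are and contribute zero. Strata containing patients of only one arm are merged across sites or surgeons within the same tumor stage. Merging is decided from arm counts only, never from the outcome.*

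This keeps the useful half of the rule and names the destination. In simulation it gave odds ratios of 2.68-2.82 against a true 2.73 without inflating type I error, and power equal to or up to 3.5 points above the written rule. The cost is one sentence and a few lines of code, with no patients and no extra data. It should be settled before R0 is analyzed by arm.

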**Methods:**

This study is a multinational, multicenter, randomized, clinical superiority trial. Patients (*n* = 262) with a GEJ type II tumor resectable by both transthoracic esophagectomy and transhiatal extended gastrectomy will be enrolled in the trial. Type II tumors are defined as tumors with their midpoint between ≤1 cm proximal and ≤ 2 cm distal of the top of gastric folds on preoperative endoscopy. Patients will be included in one of the participating European sites and are randomized to either transthoracic esophagectomy or transhiatal extended gastrectomy. The trial is powered to show superiority for esophagectomy with regards to the primary efficacy endpoint overall survival. Key secondary endpoints are complete resection (R0), number and localization of tumor infiltrated lymph nodes at dissection, post-operative complications, disease-free survival, quality of life and cost-effectiveness. Postoperative survival and quality of life will be followed-up for 24 months after discharge. Further survival follow-up will be conducted as quarterly phone calls up to 60 months.

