### Patient follow-up

The follow-up will include seven regular visits for check-up every three to six months with a total of 24 month after discharge. Further follow-up will be conducted as quarterly phone calls to determine survival up to 60 months after discharge. For a detailed listing of the procedures and items recorded in the eCRF for each trial visit, see Table 1. If a tumor recurrence is clinically suspected during the follow-up period, a CT of the thorax and abdomen as well as an endoscopy will be performed on indication to further document the disease-free survival. Loss-to-follow-up will be minimised by commissioning a person at the trial site to manage and encourage follow-up and providing of excellent and free medical care. We therefore assume a small attrition rate of 0.05 per year and study arm.

V0 Screening, V1 Baseline/Randomization, V2 Discharge, V3 + 1 month, V4 + 3 months, V5 + 6 months, V6 + 9 months, V7 + 12 months, V8 + 18 months, V9 + 24 months, Survival Follow-up up to 60 months – quarterly by phone. ^1^Negative serum pregnancy test during screening period for women of child-bearing age. ^2^Only in case of a clinically suspected tumor recurrence.

**Table 1 Tab1:** Visit schedule

	**V0**	**V1**	**V2**	**V3**	**V4**	**V5**	**V6**	**V7**	**V8**	**V9**	**Survival-** **Follow-up**
Demography	X										
Medical history	X										
Oncological history	X										
Tumor classification	X										
Pregnancy test^1^		X									
Inclusion / Exclusion		X									
Laboratory	X										
Biopsy	X										
Randomisation		X									
Physical examination	X		X	X	X	X	X	X	X	X	
Anamnesis	X			X	X	X	X	X	X	X	
Endoscopy	X				X^2^	X^2^	X^2^	X^2^	X^2^	X^2^	
CT/MRI	X				X^2^	X^2^	X^2^	X^2^	X^2^	X^2^	
Concomitant Medication	X		X	X	X	X	X	X	X	X	
EORTC QLQ-C30, −STO22, −OG 25-		X	X		X	X	X	X	X	X	
OP – Description			X								
Post-OP Complication			X								
Pathology			X								
Reference pathology			X								
AE/SAE			X	X	X						
Survival				X	X	X	X	X	X	X	X
EOS											or earlier for premature withdrawal

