### Outcome measures

The primary endpoint is overall survival, which will be followed up until 60 months after discharge of surgery. The key secondary endpoints are complete resection (R0), post-operative complications according to the Esophageal Complications Consensus Group (ECCG) definitions [18] and scored on severity by the the Clavien-Dindo classification [19], number and localization of tumor infiltrated lymph nodes at dissection, disease-free survival, quality of life (EORTC QLQ-C30, QLQ-STO22, and QLQ-OG25 after 3, 6, 9, 12, 18, 24 months) and cost-effectiveness.

After consolidation of the EORTC questionnaires data during the course of the trail, a cost effectiveness analysis of both procedures based on direct costs and resulting QALYs will be performed and the incremental cost-effectiveness ratio will be calculated. For simplification of the process, only German sites classified as excellence centers will be included into the analysis, so that consistent national costs (e.g. DRG based, medical supply, labor costs based on tariffs) can be comparable.

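### The confirmatory quality-of-life test averages scores over 36 months, but questionnaires end at 24 months, so the AUC cannot be computed as written

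*Protocol article*

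**What the plan says.** The Statistical analysis section defines the endpoint: "The secondary outcome quality of life is averaged over 36 months (area under curve, AUC"). It is then "tested for non-inferiority of the esophagectomy arm regarding a margin of 80" per cent, and gaps are handled by one sentence: "Missing values are linearly interpolated". The same section places quality of life third, after overall survival and R0 resection, in a fixed sequence meant to control the type I error at 5% two-sided.

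The data-collection text gives a different horizon:

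- Abstract, Methods: "Postoperative survival and quality of life will be followed-up for 24 months after discharge".
- Outcome measures: the EORTC instruments are scheduled up to "QLQ-OG25 after 3, 6, 9, 12, 18, 24 months".
- Patient follow-up, text: "Further follow-up will be conducted as quarterly phone calls to determine survival up to 60 months after discharge".
- Patient follow-up, visit key: "V9 + 24 months, Survival Follow-up up to 60 months – quarterly by phone". In Table 1 the EORTC row is marked at V1, V2 and V4 to V9. Its cell under survival follow-up is blank.

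**The concern.** A formal test needs an endpoint that the planned data can produce. Here the averaging window runs a year past the last questionnaire, for every patient in both arms. Interpolation joins two observed values. After V9 there is no second value, so filling months 24 to 36 would be extrapolation, for which the article gives no rule.

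This is the one quality-of-life analysis inside the alpha-controlled hierarchy, and it is the formal test behind the hypothesis that quality of life after esophagectomy is acceptable. If the window stays unresolved, someone must later truncate it at 24 months, carry the last score forward or model the missing year. These are different endpoints. The Study design section says that patient, surgeon and coordinating researcher are not blinded, so a late choice would be hard to defend as independent of the results.

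**Working it through.** **Plan's own figure.** No sample size or power is stated for the quality-of-life test, so there is no calculation to reproduce. The disputed figure is the 36-month window, and the check is to set it against the schedule.

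| Source in the protocol article | Quality-of-life horizon |
|---|---|
| Statistical analysis (AUC definition) | 36 months |
| Abstract, Methods | 24 months after discharge |
| Outcome measures | last questionnaire at month 24 |
| Table 1, EORTC row | last mark at V9, month 24 |
| Patient follow-up, text after month 24 | phone calls for survival only |

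**Share of the window without planned data.** (36 − 24) / 36 = 12/36 = 33%, in both arms.

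**Do the likely repairs give the same endpoint?** Take the trapezoid rule from discharge (month 0) over questionnaires at 0, 3, 6, 9, 12, 18 and 24 months. This start point is an assumption, since the article does not state one. V9 then carries half of the interval from 18 to 24 months, which is 3 months of weight.

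- Window cut at 24 months: V9 has weight 3/24 = 12.5%.
- V9 score carried forward to 36 months: V9 has weight (3 + 12)/36 = 15/36 = 42%.

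**How far could the average move?** As an illustration with assumed values, let the mean over 0 to 24 months be 1 and the mean over the unobserved year be x. The 36-month average is (24 × 1 + 12x)/36.

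- x = 0.8: (24 + 9.6)/36 = 0.93
- x = 1.2: (24 + 14.4)/36 = 1.07

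This range describes one arm's mean. If both arms drift by the same factor, their ratio does not change.

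**Effect on the rest of the design.** The hazard ratio is ln(0.45)/ln(0.30) = 0.663, as stated. The Schoenfeld formula gives 187 events for a fixed design, and 188 with one O'Brien-Fleming-type look at half the information, which agrees with the plan. The quality-of-life window enters neither this calculation nor the one for R0.

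**Start of the window.** Table 1 has questionnaires at V1 (before surgery) and V2 (discharge), while Outcome measures lists only months 3 to 24. V9 is counted from discharge, so an AUC from V1 to V9 would span more than 24 months. From discharge it spans 24 months, and from month 3 it spans 21.

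**The case against.** The best defence is that 36 is a slip for 24, that an average over the collected visits can be computed, and that a statistical analysis plan not shown here may already settle the matter. The first two points may well be right. The third does not remove the finding: the article states two incompatible figures, which is different from leaving a detail to another document. Nor does the Statistical analysis section rescue 36 months elsewhere. Its 36-month Kaplan-Meier time point concerns survival, and its linear mixed model is a separate analysis.

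A reader might infer that the analyst will be forced to choose a window after seeing data. The article does not support that. Its Trial status section reports four patients enrolled by May 2020, so the definition could be settled well in advance. A data-dependent choice is a risk, not a necessity.

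A reader might also infer that the non-inferiority conclusion is biased by a third. The 33% is a share of calendar time, and no effect on the treatment comparison has been shown. The V9 weights above apply only to patients who complete V9. Under the plan's assumed 2.5-year survival of 45% and 30%, many will not, and shortening the window does not settle how deaths are handled.

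Finally, the test is confirmatory only if overall survival and R0 both succeed. With 80% power for survival under the design assumptions, at least about 20% of such trials would stop before reaching it. This limits the consequence, but a test in the hierarchy must still be defined.

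Collecting questionnaires to month 36 would also remove the contradiction, but it would mean changing the schedule in every place that now says 24 months.

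**Conclusion.** The contradiction holds. The 36-month AUC cannot be computed from the planned data under the plan's own rule, because 12 of 36 months (33%) have no scheduled questionnaire in either arm. The finding rests only on the article's text and Table 1. The 12.5% and 42% weights depend on the assumed start at discharge, and the 0.93 to 1.07 range on assumed scores. They show that the repairs differ, not that the result would be wrong. The defect is a wrong window in one confirmatory secondary endpoint. It does not mean that the quality-of-life data are lost, and it leaves the overall survival and R0 tests intact.

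**What to change.** Before any quality-of-life data are examined:

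1. In the AUC definition under Statistical analysis, replace 36 months with 24 months after discharge, so that the window ends at V9. Use the same window wherever the quality-of-life hypothesis is stated.
2. State where the AUC starts, and bring the list in Outcome measures into line with Table 1. If V1 is to be part of the AUC, say so and do not describe the window as 24 months long. If V1 serves only as a baseline value, say that instead.

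This is a short text correction. It needs no new data and no change to the survival or R0 tests, the 188 events or the 262 patients. The only loss is that the claim covers 24 rather than 36 months.
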